#### Health coach introductory video call (Y/N)

Telephone coaching has been shown to produce comparable weight loss to in-person coaching [18], and supplementing a web-based programme with coaching calls improved engagement and weight loss outcomes in those that take up the call [19]. Here, participants will be offered either one call from their health coach within the first 2 weeks of the programme or will not be offered an additional call (core programme). Each call will last approximately 20 min. Participants will be sent a link to schedule a timeslot for a call with their health coach. The purpose of the call is for the health coach to introduce themselves, including their qualifications as a registered dietitian or nutritionist, and for the participant to ask any specific questions they may have about the programme. The health coaches will be trained on how to perform the calls and provided with a conversation guide to facilitate discussion.

#### Coaching drop-in webchat sessions (Y/N)

Systematic reviews have shown that frequent contact with a dietitian or therapist is associated with improved weight loss [20, 21]. Participants will either be offered or not offered (core programme) a designated 30-min time slot where their health coach will be ‘live’ in the private chat. This provides a platform for participants to receive timely responses to questions, seek guidance, and receive personalised support as well as providing regular, ongoing accountability. At the end of the first week of the programme, participants will be sent a link to schedule a timeslot to ‘drop-in’ with their health coach for personalised support delivered in the private chat function of the app. Health coaches will be able to schedule up to two participants in each 30-min session. At the scheduled time, the health coach will message the participant in the private chat to begin the session. These drop-in sessions will be offered once a week for the first month and then as required thereafter. At the end of each drop-in session, the health coach will send a booking link where the participant can schedule a suitable time for the next drop-in session. The content of the conversation will be largely led by the participant; however, the health coach will be provided with a conversation guide to prompt conversation if necessary.

#### Goal setting statement (Y/N)

Previous literature has proposed that self-determined motivation, fostered through goal setting, is associated with better weight management [22] and that monitoring goal progress is an effective strategy for promoting goal attainment [23]. Participants will either be asked to complete a goal setting statement alongside regular reflection with their health coach or will not complete a goal setting statement (core programme). Participants will be asked to complete a template in the journal section of the app, where they will be prompted to set an outcome goal (e.g., lose 5 kg by the end of the programme), a process goal (e.g., walk 5000 steps a day), and commit to performing 1–2 actions of their choice (e.g., walk to and from work every day). Participants will then be prompted at the end of each week to answer a series of reflection questions around which actions went well or not so well that week and what they might do differently next week. These reflection questions allow participants to monitor their progress and adjust their strategies accordingly. On a monthly basis, the health coach will prompt the participant to review their goal and ask them whether they wish to adjust the goal. If participants wish to adjust the goal, they will be provided with a new goal setting template to complete in the journal section of the app.

#### Food diary review and feedback (Y/N)

Previous evidence has shown that dietary self-monitoring improves weight loss [24] and that dietary self-monitoring combined with feedback leads to greater weight loss than self-monitoring alone [25]. Participants will be prompted to complete a weekly food diary and offered a review of their food diary entries by their health coach, compared to the core programme in which this occurs on an ad hoc basis. At the beginning of each week, participants will receive a reminder to complete their food diary. At the beginning of weeks 3, 6, and 10, the health coach will message in the group chat offering to review and provide personalised feedback on 1 weeks’ worth of entries for that week. Feedback will be based on Second Nature’s nutritional advice which emphasises the following: (1) Second Nature’s balanced plate model (eat three balanced meals per day, portion size guidelines), (2) base meals on whole foods (limit intake of ultra-processed foods and sugar), (3) meal planning/structure (regular meal timings, healthy snacking), and (4) fluid intake (drink at least 2 litres of water per day, limit alcohol intake, limit caffeine to before midday). Health coaches will review and send feedback to each participant via the private chat function of the app. All food diaries that participants confirm as completed will be reviewed and feedback will be provided within 1 week.

Each of these components are hypothesised to improve weight loss, either directly or in part, through enhanced engagement with the programme, and there might be some synergistic interaction between components. When individuals are provided with components that provide social support (health coach introductory video call or coaching drop-in webchat sessions) as well as components that provide accountability (coaching drop-in webchat sessions, goal setting statements, and food diary review), they will experience adequate supportive accountability, which in turn should increase programme engagement and subsequent weight loss (Fig. 2).

### Public involvement

The intervention components were developed by the researchers, healthcare professionals, dietitians, and the commercial partner. We conducted interviews with current users of the Second Nature programme to understand key barriers to programme success and user preferences, which helped to inform the selection and development of the intervention components. The acceptability and feasibility of the components in terms of perceived helpfulness for weight loss, perceived effort, and whether the components were delivered as planned, will be assessed as part of the process evaluation.

### Outcomes and measures

Outcomes and measures are presented in Table 4.

**Table 4 Tab4:** Summary of outcomes and measures

**Outcome**	**Outcome measures**
Primary	• Weight change between baseline and 16 weeks
Secondary	• Weight change between baseline and 24 weeks • Drop-out of programme between baseline and 16 weeks • Drop-out of programme between baseline and 24 weeks • Engagement with the programme between baseline and 16 weeks • Engagement with the programme between baseline and 24 weeks
Exploratory	• Weight change between baseline and 4 weeks • Drop-out of programme between baseline and 4 weeks • Engagement with programme between baseline and 4 weeks

#### Weight

Weight data will either be automatically collected using the Bluetooth weighing scales provided at the start of the programme (for those who opt to use them) or can be manually inputted into the app if participants are using their own weighing scales. Data for all participants will be retrieved from Second Nature’s database at baseline and three further time points following the start of the start of the programme: 4, 16, and 24 weeks. Participants will receive a push notification and will be instructed by a message from their health coach in the group chat to self-weigh and log their weight in the app at the end of weeks 4, 16, and 24. Participants who have not submitted a weight reading will be contacted via the private chat 3 days after the follow-up timepoint, via phone call and a further push notification 5 days after the follow-up timepoint. Data for all participants will be retrieved from Second Nature’s database. A single weight reading will be extracted for each time point by searching within a specified time (3–5 weeks for 4 weeks, 14–18 weeks for 16 weeks, and 20–28 weeks for 24 weeks), and the reading closest to the mid-point of each period will be extracted.

#### Programme drop-out

Drop-out will be defined as participants who have chosen to cancel the programme up to and including each follow-up assessment. Drop-out data will be extracted from the app aligning with each follow-up assessment: 0–4 weeks, 0–16 weeks, and 0–24 weeks.

#### Engagement

Engagement data will be collected to assess whether increased engagement with the programme mediates the association between any observed improvements in weight loss and the four components. Following the procedure used previously [17], engagement will be measured as the cumulative total number of interactions with the three main components of the app: ‘Learn’, ‘Track’, and ‘Support’. ‘Learn’ interactions will be defined as the total of number of articles read. ‘Track’ interactions will be defined as the number of times a participant viewed or had a recorded weight or steps reading. ‘Support’ interactions will be defined as the number of messages sent or received in either the private or group chat. Engagement metrics will be extracted from the app at three time periods, aligning with each follow-up assessment: 0–4 weeks, 0–16 weeks, and 0–24 weeks. The exact cut-off time point for each period will be defined based on the date of the extracted single weight reading.

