#### Secondary objectives

For the secondary outcome, the proportion of participants that drop-out from baseline to 4, 16, and 24 weeks will be assessed using logistic regression analyses.

We will also explore whether engagement acts as a mediator in the association between components and weight change. Mediation effects will also be tested for significance using the general approach described previously [28]. Engagement will be considered as a mediator if engagement significantly predicts weight and if the group effect is attenuated with adjustment for the engagement variable. The indirect effect and proportion of total effect mediated will also be calculated.

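### Support engagement counts coach messages that two of the components themselves send, and the attenuation rule can declare mediation without any effect of the component on engagement

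*Protocol article*

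**What the plan says.** **The measure.** Under Outcomes and measures (Engagement), engagement is a running total of Learn, Track and Support interactions. For Support, "interactions will be defined as the number of messages sent or received in either the private or group chat". Messages written by the coach are not excluded.

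**The period.** "Engagement metrics will be extracted from the app at three time periods, aligning with each follow-up assessment", with nominal periods of 0–4, 0–16 and 0–24 weeks. Then: "The exact cut-off time point for each period will be defined based on the date of the extracted single weight reading". The Weight section looks for that reading in windows of "3–5 weeks for 4 weeks, 14–18 weeks for 16 weeks, and 20–28 weeks for 24 weeks".

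**The components.** Drop-in sessions are held in the private chat. At the booked time "the health coach will message the participant in the private chat to begin the session", and a booking link follows each session. They are offered weekly in the first month and later on request. For food diary review, the coach posts an offer in the group chat in weeks 3, 6 and 10, and "Health coaches will review and send feedback to each participant via the private chat function of the app". The monthly goal prompt and the video-call scheduling link are described without a channel.

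**The rule.** Under Secondary objectives: "Engagement will be considered as a mediator if engagement significantly predicts weight and if the group effect is attenuated with adjustment for the engagement variable". In the same section the plan says that mediation will be tested for significance by a cited approach, and that the indirect effect and proportion mediated will be calculated.

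**The role.** Mediation by engagement is secondary objective (b). Table 4 also lists engagement to 16 and 24 weeks as secondary outcomes and to 4 weeks as exploratory.

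**The concern.** A mediator should record how participants respond to a component. Here part of the count is the component itself: a coach message that delivers a session, an offer or feedback is scored as the participant's engagement. If engagement is related to weight loss for any other reason, such as motivation, the component's effect will shrink on adjustment even when nothing passed through changed behaviour.

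The rule adds a separate weakness. It asks whether engagement predicts weight and whether the effect shrinks. It does not ask whether the component changed engagement, or whether the shrinkage exceeds chance.

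The answer to secondary objective (b), and the comparison of engagement between component levels, could then reflect the definition and chance. A smaller difficulty concerns engagement as an outcome in its own right: a cut-off tied to the weight reading does not exist for people without one.

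**Working it through.** **1. The plan's own figures.** The document gives no figure for engagement or mediation. Its power figures confirm the inputs used below: 48 groups, 15 retained per group, cluster-size SD 5, ICC 0.01, SD 4 kg, alpha 0.10. Design effect = 1 + ((1 + (5/15)²) × 15 − 1) × 0.01 = 1.157. With 360/1.157 per factor level, power for 0.75, 0.88 and 1 kg is 75.6%, 86.4% and 93.0%. With a t reference on 32 df it is 74.0%, 85.1% and 92.0%. Stated: 75%, 85%, 92%. Reproduced.

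**2. Messages written into each component.**

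| Component | Coach messages | Counted in Support? |
|---|---|---|
| Drop-in sessions | Opening message and booking link; 4 sessions in month 1 give 4 × 2 = 8, plus the conversation | Opening message yes; link only if sent by chat; all depend on booking |
| Food diary review | 3 group offers; 3 feedback messages if one per review | Offers certain; feedback depends on a completed diary |
| Goal setting | Monthly prompt | Channel not stated |
| Video call | One scheduling link | Channel not stated; negligible |

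**3. Effect on the measure.** Let X be the component, E genuine engagement (unaffected by X) and M = E + kX the recorded count, where k is the average number of component-generated messages per assigned person. With X in the model, the coefficient b of M on weight loss equals that of E. The indirect effect is therefore k × b and the direct effect falls by the same amount. With b = 4ρ/SD(E), the spurious indirect effect is 4ρk/SD(E) kg.

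**4. Effect of the rule.** In least squares, total effect = direct effect + a × b, where a is the estimated effect of X on M. For a beneficial component and b > 0, attenuation is essentially the event a > 0. If the true a is 0, its probability is one half.

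Assume SD(E) = 100 interactions and ρ = 0.2 to 0.4; neither is in the document. Then SE(a) = 100 × √(4/720) = 7.45, and P(a > 0) = Φ(k/7.45): 50% for k = 0, Φ(0.40) = 66% for k = 3 and Φ(1.07) = 86% for k = 8.

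**5. Simulation.** 48 groups of 15, ICC 0.01 for weight, SD 4 kg, a true effect of 0.75 kg acting wholly outside engagement, 1000 runs per setting. Ranges are over ρ = 0.2, 0.3 and 0.4.

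| k | Spurious indirect effect by formula, kg | Share of 0.75 kg | Attenuation rule met | Product-of-coefficients test rejects at 0.10 |
|---|---|---|---|---|
| 0 | 0 | 0% | 47–50% | 9–11% |
| 3 | 0.024–0.048 | 3–6% | 66% (formula only) | not run |
| 8 | 0.064–0.128 | 9–17% | 82–86% | 26–31% |
| 16 | 0.128–0.256 | 17–34% | 96–97% | 66–68% |

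k = 3 is the certain diary offers. k = 8 assumes that everyone attends four sessions and that the link goes by chat; at half attendance k = 4, giving 0.032–0.064 kg and Φ(0.54) = 70%. k = 16 is illustrative. Engagement was drawn without correlation within groups.

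Cleaning the measure alone leaves the rule at a coin toss (row k = 0). Changing the criterion alone still rejects too often (rows k = 8 and 16). Both changes are needed.

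**6. Cut-off.** Enrolled 48 × 30 = 1440; with a weight at the assumed 50% retention 48 × 15 = 720; without a cut-off date 1440 − 720 = 720. Among those with a reading, the furthest departures from nominal exposure are 1/4 = 25%, 2/16 = 12.5% and 4/24 = 16.7% at weeks 4, 16 and 24.

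**The case against.** Much can be said for the plan, and several stronger readings do not survive.

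- **Messages common to all arms.** A reader might count the core group messages (4×4 + 4×3 + 7×2 + 1×3 = 45 by week 16) and the reminders for missing weights as built-in mediation. Both apply in every arm and are not raised by assignment to a component.
- **Participant action.** Session messages follow a booking, and feedback follows a diary that the participant has confirmed as complete. Only the three diary offers arrive regardless of what the participant does. This stands: the increment is partly, not wholly, definitional. It is shown for two components, not four.
- **A significance test is mentioned.** It would be wrong to say that the plan computes nothing beyond attenuation. But the sentence that decides whether engagement is a mediator includes neither the test nor the indirect effect, and both would use the same count. What the cited approach requires cannot be seen.
- **At least one of four components.** A separate simulation with four inert paths gave 49–51% per component and 94% for at least one. The latter is 1 − 0.5⁴ = 0.9375, the same coin toss repeated, and it ignores that mediation is sought only where weight loss improved. It adds nothing to the per-component figure.
- **The reading-date cut-off.** Comparing window ends (18/14 = 1.29, 28/20 = 1.40) suggests a large spread, but these are extremes; participants are prompted at the target week and the reading nearest mid-window is used. Ending the count at the reading keeps the mediator before the outcome. People without a reading also lack the outcome, so the cut-off is not what removes them from a mediation analysis. The difficulty remains only for engagement as a separate outcome.
- **Limited consequence.** Mediation is described as exploratory, and components are chosen on main effects and interactions for weight. This stands.

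**Conclusion.** The point holds in a limited form. Assignment to drop-in sessions or food diary review raises recorded engagement partly by definition, and the stated criterion for mediation can be met without any effect of the component on engagement. With no such effect, it is met about half the time per component whenever engagement predicts weight. That result does not depend on the assumed SD or correlation.

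The size of the definitional part does depend on them, and on uptake: from 0.024–0.048 kg for the three certain offers to 0.064–0.128 kg for eight messages per person, against a component effect of 0.75 kg. Its direction does not, provided engagement relates positively to weight loss.

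As an outcome in its own right, 16-week engagement has no stated end date for the roughly 50% expected to lack a reading. The power figures, the primary analysis and the choice of components are not touched. The change is worth making because secondary objective (b) rests on this measure and this rule.

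**What to change.** 1. **Measure.** For the mediation analysis and the engagement outcomes, count participant-initiated actions: articles read, own tracking, messages sent. Exclude coach-sent messages. Report the protocol's present count alongside. Leaving out participants' own messages within drop-in sessions or diary feedback should be a sensitivity analysis only, since the conceptual model expects that contact to act.
2. **Criterion.** Replace attenuation with a 90% confidence interval for the indirect effect (component to engagement, times engagement to weight) that allows for clustering by group and excludes zero. The 90% level matches the plan's alpha of 0.10.
3. **Period.** For engagement as an outcome in its own right, use the nominal 4-, 16- and 24-week periods for everyone enrolled. For mediation, keep the count ending no later than the weight reading.

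Cost: a changed query on the app's logs, assuming they identify the sender, and a few sentences of wording. No new data collection is needed. The downside is some loss of comparability with the engagement definition used previously for this programme, which reporting both counts limits.

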### Sample size

The available resource allocated to this trial was 48 groups with an average of 30 participants per group. Considering the resource management principle of MOST [7], and given this allocated sample size, we calculated the available power to detect different effect sizes using the R macro %FactorialPowerPlan (Table 5).

**Table 5 Tab5:** Power calculations

**Cohen’s *****d***** effect size**	**Difference in weight**	**Power**
0.25	1 kg	92%
0.22	0.88 kg	85%
0.188	0.75 kg	75%

Power for this study is based on weight change from baseline to 16 weeks. Specifically, the study aims to assess which intervention components contribute to a more than minimal improvement in weight loss to identify components for inclusion in the optimised intervention. Our definition of at least a minimal difference in weight loss is ≥ 0.75 kg—alone or in combination with other components—at 16 weeks. We assumed a standard deviation of 4 kg from previous studies [26], which translates to a component effect size of *d* = 0.188. From a decision-priority perspective, this optimisation trial aims to screen components for an optimised intervention that could be tested in a future definitive evaluation [7, 27]. Therefore, the criteria to consider an effect important will be set liberally at *p*< .10, which is not uncommon for this phase of MOST methodology [8].

Based on previous studies, we assumed a 50% retention rate (an average of 15 participants per group) [26] and a cluster size standard deviation of 5 participants, an intraclass correlation of 0.01 and set alpha to 0.1. This sample size provides 75% power to detect a 0.75 kg difference in weight loss and 92% power to detect any differences of 1 kg or larger. Therefore, this study is powered to detect any main effects or interactions of these sizes or larger.

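### As an outcome, engagement is counted to each participant's own weigh-in date, so counting periods are unequal and, as written, people without a reading have no end date

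*Protocol article*

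**What the plan says.** Under Engagement, the protocol article says that "engagement will be measured as the cumulative total number of interactions with the three main components of the app" (Learn, Track and Support). It names nominal periods, "aligning with each follow-up assessment: 0–4 weeks, 0–16 weeks, and 0–24 weeks", and then fixes where each one ends: "The exact cut-off time point for each period will be defined based on the date of the extracted single weight reading".

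Under Weight, the search windows for that reading are "3–5 weeks for 4 weeks, 14–18 weeks for 16 weeks, and 20–28 weeks for 24 weeks", and the reading nearest the middle of the window is taken. Participants are prompted to weigh at the end of weeks 4, 16 and 24. Late weighers are chased: "Participants who have not submitted a weight reading will be contacted via the private chat 3 days after the follow-up timepoint", then by phone and a further push notification at 5 days.

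Table 4 lists engagement to 16 weeks and "Engagement with the programme between baseline and 24 weeks" as secondary outcomes, and engagement to 4 weeks as exploratory. Secondary objective (b) and the Secondary objectives part of the Statistical Analysis section use engagement as a mediator of the component effects on weight.

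For the 16-week weight endpoint, the Sample size section says "we assumed a 50% retention rate (an average of 15 participants per group" and a total of 48 groups averaging 30. Programme drop-out is also extracted from the app for the same three periods, but with no link to the weight date.

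**The concern.** A cumulative count can be compared between randomised groups only if everyone is counted over the same period, or if the count is adjusted for period length. Here the end of the period is something the participant does after randomisation, and no adjustment is stated. The components work through coaching contact, goals and accountability, so they may well change whether and when people weigh themselves. A component could then shift the engagement outcome through the timing or presence of a weight reading, without changing how much the app is used.

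There are two consequences. Among people with a reading, periods differ in length. People without a reading have no end date under the stated rule, so applying it literally leaves a comparison among weight-reporters, a group formed after randomisation. A secondary outcome is at stake, together with the Abstract's stated aim of exploring which components improve engagement. The primary weight outcome is not affected.

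**Working it through.** **Step 1. What the 50% refers to.** Inputs from the Sample size section: 48 groups, 15 retained per group, cluster-size SD 5, ICC 0.01, alpha 0.10 (taken as two-sided), SD 4 kg.

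- Retained for the weight analysis: 48 × 15 = 720.
- Coefficient of variation of cluster size: 5/15 = 0.333.
- Design effect: 1 + ((0.333² + 1) × 15 − 1) × 0.01 = 1.1567.
- Effective sample size: 720/1.1567 ≈ 622, split equally between the two levels of a component.

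| Effect size | Stated power | Normal approximation | Noncentral F, 46 df |
|---|---|---|---|
| 0.188 (0.75 kg) | 75% | 75.8% | 74.7% |
| 0.22 (0.88 kg) | 85% | 86.4% | 85.5% |
| 0.25 (1 kg) | 92% | 93.0% | 92.3% |

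The stated power is reproduced to within 2 points. The plan therefore does treat 720 as the number contributing a 16-week weight.

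**Step 2. Participants without a week-16 end date.** Planned total: 48 × 30 = 1440. Without a reading at 50%: 1440 × 0.5 = 720. Over the planned range of group sizes: 48 × 28 = 1344 gives 672, and 48 × 32 = 1536 gives 768. No corresponding assumption is given for weeks 4 or 24.

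**Step 3. Spread of counting periods among those with a reading** (windows from the Weight section).

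| Time point | Shortest | Longest | Ratio | Departure from nominal |
|---|---|---|---|---|
| 4 weeks | 3 | 5 | 5/3 = 1.67 | ±25% |
| 16 weeks | 14 | 18 | 18/14 = 1.29 | ±12.5% |
| 24 weeks | 20 | 28 | 28/20 = 1.40 | ±16.7% |

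**Step 4. What period length alone does to the score.** Messages received count as Support. The core programme's minimum group-message schedule is 4 a week in weeks 1–4, 3 in weeks 5–8, 2 in weeks 9–15, 3 in weeks 16–17, then at least 2 in the Growth phase. Cumulative minimum:

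- 3 v 5 weeks: 3 × 4 = 12 v 16 + 3 = 19.
- 14 v 18 weeks: 16 + 12 + (6 × 2) = 40 v 16 + 12 + 14 + 6 + 2 = 50.
- 20 v 28 weeks: 50 + (2 × 2) = 54 v 50 + (10 × 2) = 70.

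These differences arise for a participant who does nothing, purely from where the count stops. In addition, someone who has not weighed by 3 days after the time point receives a private message, which is itself a Support interaction and falls inside a count that is still running.

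**Step 5. A more typical lateness.** A reading 5 days late lengthens the period by 5/28 = 17.9% at week 4, 5/112 = 4.5% at week 16 and 5/168 = 3.0% at week 24.

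**The case against.** The strongest defence is that the rule suits the mediation analysis. Ending the count at the weight date keeps the mediator before the outcome. If the rule were simply deleted and day 112 used for everyone, a participant whose extracted weight fell at week 14 would have two weeks of post-outcome engagement in the mediator. A week-20 reading would bring in four weeks at the 24-week point. This stands, and it is why the rule should stay for mediation.

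Second, the window ratios are extremes. Prompts at the time points, reminders, and the choice of the reading nearest the mid-point should pull most periods towards nominal, and frequent weighers will usually be close to it. This also stands. At 16 and 24 weeks the typical distortion is probably a few per cent.

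Third, the article does not say that people without a reading are excluded, and a fuller document may hold a fallback for them. That is a fair limit on the missing-end-date part. It does not cure the unequal periods, which follow from a rule that is stated.

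A reader might go further and infer that:

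- half the sample is lost at every time point, although the 50% is a planning assumption for week 16 only;
- app logs are complete for all participants, although the article says only that metrics come from the app, and participants may ask for their data to be deleted;
- those without a reading are the least engaged, which is plausible but not stated.

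The documents do not establish any of these.

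**Conclusion.** The point holds for engagement as an outcome, not as a mediator. As written, a listed secondary outcome is an unadjusted count over a period set by weighing behaviour after randomisation. The spread is at most 1.67-, 1.29- and 1.40-fold at 4, 16 and 24 weeks, and usually smaller. At week 16 the rule supplies no end date for about 720 of 1440 participants (672–768 over the planned range), provided the 50% assumption holds and no fallback exists elsewhere.

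It would be too strong to say that engagement is invalid as an outcome, or to quote a bias in interactions. The documents give no mean or SD for engagement and no distribution of weigh-in dates, so the size of any bias in a component effect cannot be derived. What can be said is that the comparison is open to selection and period-length effects that app data do not impose, because the counts do not depend on a weight being logged.

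**What to change.** Define engagement twice, by purpose.

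- **Outcome:** count interactions from programme start to fixed days 28, 112 and 168 (4, 16 and 24 × 7) for every randomised participant with app data, whether or not a weight was logged. Those who cancel keep the count they have accrued.
- **Mediator:** keep the cut-off at the date of the extracted weight reading, for the mediation analysis only, and say so.

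This needs one or two sentences in the Engagement section and two engagement extractions instead of one. It needs no new data collection and leaves the power for weight unchanged. The Data management section says data go to the researchers after study completion, so the extraction rule can be settled before that transfer.
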